**Methods and Planned Analysis::**

This multicenter stepped-wedge cluster (nested) randomized controlled trial aims to recruit 945 nulliparous pregnant individuals. The trial is conducted in two phases. During Phase 1, control group participants are under standard care. During Phase 2, participants are randomized to ACE instruction via a pre-recorded online video or a one-on-one session with a midwife. Adjusted logistic regression analysis will be used to examine the relationship between ACE instruction and breastfeeding outcomes.

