### Sample Size

The research team has used a control group estimate for the primary outcome, EBF4M, of 27% based on the Australian National Infant Feeding Survey (Australian Institute of Health and Welfare, 2011). This represented the best available, nationally representative breastfeeding data at the time of study design.

The research team hypothesized that an EBF4M rate of 45% will be achieved in both intervention groups. An alpha of 0.05 has been selected for the sample size calculations as (1) the tests are one-sided and (2) there are two primary hypothesis tests to be carried out. An *n* of 271 per group will be required to have over 80% power to detect a difference between the MW and VI groups, independently, as well as the control group. This will demonstrate superiority by a margin of at least 5% based on a difference in proportions using the normal approximation with an intraclass correlation of 0.01. With this *n* (271) in both the MW and VI groups, and assuming a rate of 45% will be observed for EBF4M within both intervention groups, the trial will have 80% power to demonstrate non-inferiority with a lower equivalence rate of 32%; based on the difference in proportions using the normal approximation. This lower equivalence rate was deemed acceptable as it represents the same increase over the control group as the primary analysis (i.e., 5%). Data will be analyzed based on the principles of intention to treat and per-protocol analysis, with non-inferiority concluded if both analyses produce the same results (Angeli et al., 2020; Tripepi et al., 2020). A loss to follow-up rate of 15% is anticipated; therefore, the research team estimates that 315 pregnant individuals will be recruited into each group to achieve sufficient follow-up data for analysis. Rolling recruitment across multiple hospital sites will be required to achieve the recruitment target of 945 participants.

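### Recruiting 315 per group allows for about 14% loss to follow-up, not the stated 15%: a minor arithmetic slip with negligible effect on power

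*Protocol article*

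**What the plan says.** All the figures are in one paragraph, the Sample Size section of the protocol article.

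- Required size: an n "of 271 per group will be required to have over 80% power".
- Attrition and recruitment: "A loss to follow-up rate of 15% is anticipated; therefore, the research team estimates that 315 pregnant individuals will be recruited into each group". The second half is drawn as a conclusion from the first.
- Total: recruitment runs across several sites to "achieve the recruitment target of 945 participants". The abstract repeats this: the trial "aims to recruit 945 nulliparous pregnant individuals".

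The section gives no inflation formula and no rounding rule. The other inputs to the power calculation, in the same section, are 27% exclusive breastfeeding at 4 months under control and 45% under either intervention, a superiority margin of 5 percentage points, an intraclass correlation of 0.01, and a non-inferiority limit of 32%. On alpha: "An alpha of 0.05 has been selected for the sample size calculations as (1) the tests are one-sided".

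**The concern.** The text presents 315 as the consequence of needing 271 and losing 15%. With both inputs printed, one division checks it, and the check fails: 315 is below the number needed to retain 271. An attrition allowance exists to protect the required number, so rounding it down defeats its purpose.

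What is at stake is mainly the coherence of the sample size justification. A reader who takes the paragraph at its word expects 271 per group with 4-month data if attrition runs as forecast, and would find about 267 or 268. Whether that also matters for power has to be computed.

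**Working it through.** **1. Inputs.** From the Sample Size section: 271 required per group, 15% loss, 315 recruited per group, 945 in total, and the rates, margin, alpha and intraclass correlation listed above. The 271 is taken as given. It cannot be rebuilt uniquely, because the number and size of clusters behind the intraclass correlation adjustment are not stated.

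**2. Trying to reproduce 315.**

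- Standard inflation, n/(1 − d): 271/0.85 = 318.82, so 319. Total 3 × 319 = 957. Check: 319 × 0.85 = 271.15.
- Common shortcut, n × (1 + d): 271 × 1.15 = 311.65, so 312.
- The stated 315 lies between the two and matches neither. The total is consistent with it: 3 × 315 = 945.

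**3. What 315 delivers.**

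- Per group: 315 × 0.85 = 267.75, which is 3.25 below 271 (1.2%).
- Overall: 945 × 0.85 = 803.25 against 3 × 271 = 813.
- Loss at which 315 still leaves 271: 1 − 271/315 = 13.97%.
- Recruits short of the exact figure: 4 per group (4/319 = 1.3%) and 12 overall.

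**4. Effect on power.** Unpooled normal approximation, one-sided alpha 0.05, one intervention arm against control, with n per group:

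Power = Φ[(0.45 − 0.27 − 0.05)/SE − 1.645], where SE = √[(0.27 × 0.73 + 0.45 × 0.55) × DE/n].

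DE = 1 without clustering. With k equal clusters per group, DE = 1 + (n/k − 1) × 0.01. Non-inferiority uses the same form with 45% in both arms and a margin of 45 − 32 = 13 points. The plan names the intraclass correlation only for the superiority calculation; applying it to non-inferiority is an assumption. Every value of k is an assumption too.

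| Clusters assumed | Superiority, n = 271 | n = 268 | Non-inferiority, n = 271 | n = 268 |
|---|---|---|---|---|
| none (DE = 1) | 94.1% | 93.9% | 91.9% | 91.6% |
| 7 | 86.2% | 86.0% | 82.8% | 82.6% |
| 6 | 84.8% | 84.6% | 81.3% | 81.0% |
| 5 | 82.9% | 82.6% | 79.2% | 78.9% |
| 4 | 79.97% | 79.7% | 76.1% | 75.9% |

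Worked example for seven clusters, superiority. At n = 271, DE = 1 + (271/7 − 1) × 0.01 = 1.377 and SE = 0.0475, giving 86.2%. At n = 268, DE = 1.373 and SE = 0.0477, giving 86.0%.

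In every row the fall is 0.2 to 0.3 percentage points. The level of power depends strongly on the assumed cluster number; the change due to the slip hardly does.

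**5. The primary comparison.** Tables 1 and 4 define the primary outcome as control against both intervention groups combined. With the same formula, two intervention participants per control and no clustering, power goes from 98.35% at 271 per group to 98.27% at 268. These calculations ignore period effects of the stepped-wedge design.

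**The case against.** **It is only rounding.** The 315 is within 1.3% of 319 and lies between the results of the two usual formulas. The 15% is a forecast, the 315 is called an estimate, and a loss of 14% instead of 15% is well within the uncertainty of any such forecast. This stands as far as importance goes, and it is why the point is minor. It does not make the sentence right: no rounding rule turns 318.8 into 315, and the text derives one figure from the others.

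**The number analysed need not be 315 × 0.85.** The plan analyses by intention to treat as well as per protocol, and the Planned Data Analysis section allows multiple imputation if missing data prove problematic. That is fair. It is a reason to speak of participants with follow-up data and not of analysable participants. It leaves the division unchanged.

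**The tempting stronger reading.** A reader might infer that the shortfall takes the trial below its 80% power. The documents do not support this. The only row above in which superiority power appears to cross that line assumes four clusters, a number stated nowhere; the Setting section lists seven proposed sites. With four clusters, power is 79.97% even at the full 271, so that scenario never meets the plan's claim of more than 80%, and the 315 is not the cause. Likewise, the non-inferiority values below 80% for four and five clusters are already below it at 271. They reflect the assumed cluster number, not the attrition slip.

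**Conclusion.** The arithmetic error is real and minor. As printed, 271 per group, 15% loss and 315 per group do not fit together: 315 leaves about 267 to 268 after 15% loss, and keeping 271 needs 319 per group (957 in total). Nothing elsewhere in the article repairs this. This part rests only on figures that the article prints.

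The consequence is negligible: 0.2 to 0.3 percentage points of power without clustering or with four to seven equal clusters, given the plan's own rates, margins, alpha and intraclass correlation. The slip gives no ground for calling the trial underpowered or for raising the recruitment target. Whether 271 is itself adequate under clustering is a separate question, which cannot be settled without the cluster number.

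**What to change.** Keep 945 and correct the sentence in the Sample Size section in one of two ways:

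1. State that 315 per group allows for about 14% loss to follow-up while retaining 271; or
2. Keep the 15% and state that about 267 per group will then have follow-up data, with the power for that number calculated from the cluster number that the team actually assumed, and that cluster number given.

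The first is the shorter correction. The second is more informative, because it also lets a reader check the power statement.

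The cost is one sentence, plus one short power calculation under the second option. No extra participants are needed, and neither the design nor the analysis changes.

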## Data Collection and Monitoring

### Antenatal Period

All participants receive a health check via telephone between 35 and 36 weeks gestation. An ACE Study researcher administers the short health check survey to determine if a participant has developed any health conditions during pregnancy that are part of the exclusion criteria. After completion of the health check survey, participants in the intervention groups receive the ACE intervention between 36 and 37 weeks gestation. For participants in the VI group, the ACE instruction is illustrated in the ACE video where information is delivered by an IBCLC. VI group participants receive the link to the video via email. The study midwives/IBCLCs delivering the one-on-one instruction are provided with a written overview of the relevant ACE information to discuss with participants prior to conducting an instruction session. Study midwives/IBCLCs are provided with a checklist to complete during each instruction session to ensure all teaching points are covered, and the ACE technique has been demonstrated with either a knitted breast or hands-on assistance and practice (if the participant agrees). The checklist is available in the online Supplemental Material.

#### Antenatal Colostrum Expression Instruction

Intervention group participants are instructed to commence hand expressing from 37 weeks gestation, twice a day for 3–5 min per breast (maximum 10 min), using the accepted breast expression technique detailed below (Australian Breastfeeding Association, 2023). Participants are instructed to begin by stroking the breast towards the nipple and gentle breast massage to help stimulate the milk ejection reflex. Further instruction is given to make a “C” shape with the thumb and index finger and place approximately 3–4 cm on either side of the nipple, pressing in towards the chest and then pressing the fingers together and gently rolling fingers forward, being careful not to squeeze or pinch the nipple. Participants are advised to repeat the process to build up a rhythm, rotate the position of the fingers and thumb around the areola, and repeat the expressing technique to stimulate and remove colostrum from different parts of the breast. Participants are advised that small drops of colostrum may glisten on the nipple and can be collected using a sterile syringe. Participants are informed colostrum may not bead on the nipple and are reassured that this is not an indicator of potential breastfeeding ability or postpartum milk production.

Participants are provided with an intervention pack that contains a one-page handout outlining key points to remember when practicing ACE, 15 × 1 ml syringes to collect colostrum, and a cooler bag. Intervention packs can be collected from antenatal clinics at trial sites or from the midwife/IBCLC providing the one-on-one instruction. Participants are instructed to use one or more syringes for colostrum collection per day and to keep the syringes in the fridge between uses. Participants are informed that the syringes should be labelled with the date of collection, placed in a zip lock bag, and stored in their home freezer at the end of each day. Participants are provided with a bag labeled with their name to transport the colostrum syringes to the hospital at the time of birth and advised to transport the colostrum in the provided cooler bag with a freezer block. At the trial sites, there is an ACE Study box in the freezers on the maternity wards for participants to store their antenatal colostrum. After birth, the antenatally expressed colostrum can be used to supplement breastfeeding if required. If breastfeeding is going well, expressed colostrum may not be required. If colostrum syringes are not required at birth, they can be stored for 3 months in the freezer section of a refrigerator with a separate door, or 6–12 months in a deep freezer. If thawed, colostrum should be used within 4 hours if kept at room temperature, or within 24 hours if kept in the refrigerator (Australian Breastfeeding Association, 2022).

If COVID-19-related issues mean that in-person consultations are not possible, one-on-one sessions with a midwife/IBCLC may take place online. This will be noted in the data collection and when reporting findings.

Participants in the MW and VI groups are provided with direct access to an electronic milk expressing diary via Research Electronic Data Capture (REDCap; Harris et al., 2019). The diary can be accessed by email link sent daily to participants and is used to record the date they start ACE, the time they express, the volume of colostrum expressed per day, and reasons for not expressing if that occurs. The milk expressing diary has a section for additional comments where participants are encouraged to record their feelings about expressing (feelings about obtaining colostrum or not), the number of times they watch the video at home (if in the VI group), and the absence or presence of uterine contractions.

During pregnancy, participants complete the mothers’ antenatal questionnaire (MAQ) online, which is used to collect demographic information, maternal health information, breastfeeding intentions, maternal attitudes towards infant feeding, and breastfeeding self-efficacy.

### Medical Data

With consent, participants’ medical and obstetric outcome data, infant feeding method at first feed, the administration of any human milk substitutes in the hospital, and infant feeding method at hospital discharge are obtained from medical records by a research assistant.

### Postnatal Follow Up

Postnatal questionnaires are administered via telephone by a research assistant at 1, 4, 8, 12, and 16 weeks postpartum to assess infant feeding methods and/or reasons for ceasing breastfeeding. Definitions of infant feeding methods used for the ACE Study are described in Table 2. Participants’ contact points and assessments are shown on the participant timeline in Table 3.

**Table 2. table2-08903344231215074:** Definitions of Infant Feeding Methods Used for the ACE Study.^
1
^

Feeding Method	Infant Receives	Infant May Also Receive	Infant Does Not Receive
Exclusive breastfeeding	Human milk (including expressed human milk)	Oral hydration solutions, drops, syrups (vitamins, minerals, medicines)	Anything else (including water and herbal fluids)
Breastfeeding fully	Human milk (including expressed human milk)	Occasional liquids (water, water-based drinks, and juice). Oral hydration solutions, drops, syrups (vitamins, minerals, medicines)	Anything else (in particular, human milk substitutes, e.g., formula)
Combination (mixed) feeding	Human milk (including expressed human milk) and human milk substitutes	Occasional liquids (water, water-based drinks, and juice). Oral hydration solutions, drops, syrups (vitamins, minerals, medicines)	Anything else
Human milk substitute feeding	Human milk substitutes (bottle-fed)	Occasional liquids (water, water-based drinks, and juice). Oral hydration solutions, drops, syrups (vitamins, minerals, medicines)	Anything else
Other	Not specified. May include human milk substitutes (tube feeding)	Anything else	

*Note*. ACE = antenatal colostrum expression.

1 Based on the WHO Indicators for assessing infant and young child feeding practices: Definitions and measurement methods (2021).

**Table 3. table3-08903344231215074:** The ACE Study Participant Timeline.

Timepoint	Study Period									
	Enrollment	Allocation	Post-allocation							Close-out
	*-t_1_*	0	*t_1_*	*t_2_*	*t_3_*	t_4_	*t_5_*	*t_6_*	*t_7_*	*t_x_*
Enrollment										
Eligibility screen	X									
Informed consent	X									
Allocation		X								
Intervention										
MW				X						
VI				X						
Controls										
Assessments										
Demographics			X							
IIFAS			X							
BSES-SF			X				X			
Health check				X						
Colostrum sample					X					
Secretory activation						X				
Medical records						X				
Exclusive BF										
Process evaluation										X

### Colostrum Samples

The research team will conduct exploratory work in a subgroup of participants in the trial who are invited to provide colostrum samples for this optional, opt-in part of the trial. This data will help determine whether expressing colostrum in pregnancy has any effect on colostrum composition after birth. The research team intends to analyze post-birth colostrum samples from 35 individuals in the control group and 35 individuals from each of the intervention groups (total 70 intervention participants). This subset of participants is invited to provide two postnatal colostrum samples of no more than 1 ml each, within the first 24 hours postpartum (see the online Supplemental Material).

### Process Evaluation

A subset of participants will be invited to participate in the process evaluation which is nested within the trial to ascertain participants’ views on the acceptability of the ACE instruction and education received. This will inform future use of the ACE instructional video for teaching hand expression in pregnancy. The process evaluation will be used to understand the process that took place during participation in the ACE Study and to understand participants’ thoughts and views around expressing colostrum in pregnancy. Data will be collected using a set of standardized questions with Likert scale responses, as well as open-ended questions. The short survey will be added to the end of the 4-month post-birth questionnaire and be administered either over the telephone or as an online survey. If done over the telephone, the researcher will ask the participant if the conversation can be voice recorded to assist in capturing all relevant data when typing in responses. The recording will be deleted once the survey has been filled out by the researcher. Participants can decline to be voice recorded and still complete the survey over the telephone. Recording will be conducted using Teams if the participant provides verbal consent for this. Teams will generate a transcript of the conversation as well as an audio recording. The recording and transcription will be deleted after the data has been transferred to the survey and it is complete. The process evaluation survey will take approximately 5–10 min to complete.

Quantitative data will be analyzed using Qualtrics. Open-ended questions will be analyzed thematically and reported using the consolidated criteria for reporting qualitative research (COREQ) checklist. To ensure anonymity, data will de-identified and pseudonyms will be used to maintain confidentiality.

### Current Trial Status

The trial is ongoing and in the data collection phase. Recruitment began in September 2019, with an anticipated finish date of end. The last recruited participants are expected to reach the primary endpoint of 4 months postpartum in April 2025. Completion of data analysis is anticipated by the end of 2025.

### Informed Consent

The electronic consent form must be completed and signed before the participant is enrolled in the trial (see the online Supplemental Material). Participants who agree to donate samples of colostrum for analysis must complete an additional consent form to release the samples from the hospital sites to the trial.

### Data Management

Participants are informed before enrollment that their information will be kept confidential. The principal investigators, trial biostatistician, data monitoring committee (DMC) members, and the first author conducting the primary analysis will have access to the data. Personal demographic information, medical data obtained from medical files, and questionnaire data provided by participants will be reported anonymously. All data generated or analyzed during the current trial are not publicly available, although other investigators may request access to the dataset if a formal request describing their plans is approved by the principal investigators and the relevant ethics approval is in place.

Research records from the ACE Study will be retained for a minimum of 25 years from the date of publication or conclusion of the trial, whichever is later. Hard copies of eligibility screening forms and any other sensitive data are securely stored in a locked cabinet in an access-controlled area in the School of Medical and Health Sciences at ECU, Joondalup Campus. Only the ACE Study investigators have access to these files.

All data is managed using REDCap, an electronic data capture tool, hosted at Telethon Kids Institute. REDCap is a secure, password-protected, web-based software platform designed to support data capture for research studies, providing (1) an intuitive interface for validated data capture; (2) audit trails for tracking data manipulation and data export; (3) automated export procedures for seamless data exports in common statistical package formats; and (4) procedures for data integration and interoperability with external sources (Harris et al., 2019).

### Data Monitoring

The DMC members have been appointed with an external chair to provide an independent assessment of the safety and validity of the trial. The role of the DMC is to safeguard the interests of the trial participants and review accumulating data from the ongoing trial to assess (at regular intervals) the progress and integrity of the trial, the safety data, and the efficacy of the primary endpoint (Ellenberg et al., 2019) The DMC acts in an advisory role and provides recommendations to the principal investigators where applicable. A trial-specific charter has been formed with clear operating procedures, including the schedule and format of DMC meetings, how trial data will be presented at meetings, who has access to preliminary data, who will attend meetings, and a plan for the presentation of preliminary reports. DMC meetings are divided into open and closed sessions so the investigator (blinded to group allocation) with intimate knowledge about the progress of the trial, can attend to share information about the trial while maintaining the confidentiality of preliminary analysis results presented in closed sessions.

